#### 2.1.2. Enhanced Treatment-as-Usual Control Group

Participants from the enhanced treatment-as-usual (eTAU) control group will receive the usual care that is provided to adults with ADHD across clinical settings in Malaysia, along with a 30 min online psychoeducation webinar on adult ADHD. The participants will be allowed to initiate, maintain, or discontinue a treatment as they wish. We play no role in determining the treatment plan of the participants. However, we will emphasize the importance of seeking treatment as needed from their respective clinicians throughout the trial. The participants will be required to report both pharmacological and non-pharmacological treatments that they have received through an online questionnaire during the trial period. Data from the eTAU control group participants receiving either mindfulness-based intervention or CBT from their treating clinicians during the trial period will be excluded from statistical analysis to avoid data contamination. The participants from the eTAU control group will receive an invitation to participate iMBI upon completion of data collection.

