### 2.5. Sample Size

Sample size estimation is based on a meta-analytic approach. This estimation includes mindfulness-based intervention studies of individuals with ADHD published from 2008 to 2019 [41,52,53,54,55]. Using a power of 80%, *α* = 0.05, and effect size *f* = ½ *d*, the sample size for the present study is estimated. For inattention, Cohen’s *d* ranges from 0.33 to 3.14. For hyperactivity–impulsivity, Cohen’s *d* ranges from 0.24 to 1.32. For executive functioning, Cohen’s *d* ranges from 1.08 to 2.16. For all treatment outcome variables, it is suggested that a sample size of 45 per condition is needed to detect a power of 0.80 and *α* = 0.05. The present study anticipates a 20% attrition rate, so a sample size of 54 participants per condition is needed, totaling 108 participants.

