### 2.11. Data Analysis

Data will be analyzed by using the IBM Statistical Package for the Social Sciences (SPSS) version 27(IBM, Armonk, NY, USA). Multivariate analysis of covariance (MANCOVA) will be employed to assess mean differences of outcome variables at immediate post-intervention and 1-month follow-up between the two groups (i.e., iMBI + TAU vs. eTAU) simultaneously with baseline scores as covariates. Pairwise comparisons will be conducted to identify specific differences between the groups as deemed necessary. Statistical significance is set at *p* < 0.05. The magnitude of the effect size will be reported using Cohen’s *d* value. When necessary, study data will be analyzed using intention-to-treat analysis (ITT). For ITT, the last observation carried forward method will be used to impute missing values or dropouts. We will perform per-protocol analysis to examine the effectiveness of iMBI when implemented in an optimal manner.

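### The as-randomised analysis is made conditional with no stated trigger, no analysis set is named for the MANCOVA, and some controls are excluded after randomisation

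*Protocol article*

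**What the plan says.** Section 2.11 gives the main model: "Multivariate analysis of covariance (MANCOVA) will be employed to assess mean differences of outcome variables at immediate post-intervention and 1-month follow-up", comparing the two arms with baseline scores as covariates. It does not say which participants enter the model.

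The as-randomised analysis then appears with a condition: "When necessary, study data will be analyzed using intention-to-treat analysis (ITT)". The next sentence gives its imputation rule: "For ITT, the last observation carried forward method will be used to impute missing values or dropouts". The per-protocol analysis carries no condition: "We will perform per-protocol analysis to examine the effectiveness of iMBI when implemented in an optimal manner". No sentence ranks these analyses. The threshold is given once: "Statistical significance is set at *p* < 0.05".

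Section 2.1.2 adds a rule for the control arm. Data from eTAU participants who receive a mindfulness-based intervention or CBT from their clinicians "during the trial period will be excluded from statistical analysis to avoid data contamination". The same section says of treatment: "The participants will be allowed to initiate, maintain, or discontinue a treatment as they wish".

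Section 2.5 plans for losses: "The present study anticipates a 20% attrition rate".

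**The concern.** Randomisation protects the comparison of everyone randomised, in the arms to which they were allocated. Section 2.11 makes that comparison optional and the per-protocol comparison certain. Because the condition has no trigger, whether ITT is needed can be judged only after dropout is known, and nothing in the text stops it being judged after the results are known. With 20% attrition planned, the candidate sets will differ and may disagree. The text does not say which one then carries the conclusion.

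The section 2.1.2 exclusion compounds this. It depends on what participants do after randomisation, it applies to one arm, and it is not limited to a secondary analysis. Read literally, it also applies to the analysis labelled ITT, so no analysis in the article is clearly a comparison of all 108 participants.

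This is more than detail left to an analysis plan. The article states a rule for the analysis set. An analysis plan that followed it would inherit the discretion, and one that did not would contradict the published protocol.

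**Working it through.** **1. The plan's own figures (section 2.5).** 45 per arm before attrition; 45 × 1.20 = 54 per arm, 108 in total, as stated. (Dividing instead gives 45 / 0.80 = 56.25, so 57 per arm. That is a separate matter and nothing here rests on it.) Expected loss is 0.20 × 108 = 21.6 participants, leaving 54 × 0.80 = 43.2 per arm. A completer set would therefore omit about 22 of the 108.

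**2. The analysis sets side by side.**
- MANCOVA (2.11): set not named.
- ITT with last observation carried forward (LOCF) (2.11): conditional, trigger not given.
- Per-protocol (2.11): unconditional.
- Removal of eTAU participants who receive mindfulness or CBT (2.1.2): unconditional, control arm only.
- Analysis that carries the conclusion: not stated.

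**3. Cost of choosing the set after the results.** Simulation of one outcome at one time point by ANCOVA on baseline, 20,000 trials. From the documents: 54 per arm, 20% loss, p < 0.05 (taken as two-sided). Assumed: no true effect, baseline-outcome correlation 0.5, loss at random, and a per-protocol set that removes a further 20% of iMBI at random. The last two lines assume an analyst who always reports a significant set if there is one.
- Completers alone: 5.2% false positives.
- ITT with LOCF alone: 5.1%.
- Whichever of those two is significant: 6.3% (repeat runs 6.2 to 6.4%).
- Any of the three sets: 7.7% (repeat runs 7.6%).

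The excess over 5% is thus about 1.3 percentage points with two sets and 2.6 with three.

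**4. Is bias from selective dropout part of this point?** Same set-up, control loss at random, but iMBI loss correlated 0.3 or 0.5 (assumed) with a worse outcome. Each pair below gives the result at 0.3 / 0.5.

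Loss related to the part of the outcome not explained by baseline:
- Spurious benefit: completers 0.088 / 0.153 SD; LOCF 0.069 / 0.123 SD. LOCF keeps 0.069 / 0.088 = 78% and 0.123 / 0.153 = 80%.
- False positives: completers 7.7% / 12.8%; LOCF 7.4% / 12.1%.

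Loss related to the outcome itself:
- Spurious benefit: completers 0.081 / 0.131 SD; LOCF 0.043 / 0.068 SD. LOCF keeps 0.043 / 0.081 = 53% and 0.068 / 0.131 = 52%.
- False positives: completers 7.3% / 11.5%; LOCF 5.9% / 7.8%.

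Making the documented ITT analysis unconditional would therefore leave roughly half to four-fifths of this bias in place.

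**The case against.** The strongest reply is that the condition simply means that ITT is run if values are missing. The sentence that follows ties ITT to missing values and dropouts, and with 20% attrition planned the analysis would then be run. That is a natural reading, but the text does not say it. It would also leave the condition with little purpose, rank no set above another, and not restore the controls removed under section 2.1.2. If it is what the sponsor meant, deleting the condition loses nothing.

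Several stronger readings are tempting and the documents do not support them.
- A reader might infer that only selected sets are guaranteed. The MANCOVA set is unnamed; it is not stated to be a completer set. What can be said is that section 2.1.2 selects it at least in part.
- A reader might infer that people who stop iMBI drop out of the MANCOVA even if they give outcome data. They would not. Listwise deletion, which is software behaviour and not a statement in the article, removes only those with missing scores. Only the per-protocol set could omit stoppers who were measured, and section 2.11 gives that analysis a separate purpose.
- A reader might infer that unblinded staff will decide whether ITT is needed. Sections 2.2 and 2.3 describe a single-blind trial with participants blinded. They do not say who makes this decision or what that person will have seen.

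It is also fair that section 2.10 already requires participants to complete all measures and schedules outcomes at all three times without limiting this to those who adhere.

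**Conclusion.** The point stands as a badly fixed rule: an undefined condition on the as-randomised analysis, no named set for the main model, an unconditional per-protocol analysis, and an exclusion after randomisation in one arm.

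Its measurable size is modest: about 6.3% false positives when choosing between completers and ITT with LOCF, and about 7.6% with a per-protocol set added, against 5%. These figures assume random loss, a baseline correlation of 0.5, a single outcome and an analyst who always takes the significant result. No size is given for the section 2.1.2 exclusion, because the article does not say how many controls it might remove.

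A reader might also count the 0.08 to 0.15 SD of spurious benefit under selective dropout as harm from the conditional ITT. That would be wrong. The dropout correlations are assumptions, and LOCF keeps much of the bias, so it belongs mainly to the missing-data method. The case for the change rests on making the headline result a randomised comparison fixed in advance, not on those figures.

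**What to change.** In section 2.11 and in the analysis plan:
- Delete the two-word condition that opens the ITT sentence.
- State that the primary analysis includes all randomised participants in their allocated arm, whatever they received or completed, and that the conclusion rests on it. Per-protocol and completer analyses are supportive and cannot replace it.

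In section 2.1.2, keep eTAU participants who receive mindfulness or CBT in the primary analysis and apply the exclusion only in a supportive analysis. Without this, the new primary set would contradict section 2.1.2.

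In section 2.10, state that week 8 and week 12 measures are collected from participants who stop iMBI.

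The cost is a few sentences, with no extra participants or measures; the only added effort is following up those who stop. The estimate may come out slightly less favourable to iMBI. The missing-data method needs its own attention, because this change does not settle it.

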### 2.2. Study Design

This is a single-blind randomized controlled trial. Participants who fulfil the inclusion and exclusion criteria will be randomly assigned to an 8-week online mindfulness-based intervention plus treatment-as-usual (TAU) group (i.e., iMBI + TAU) or an eTAU control group using a simple randomization technique. Inattention, hyperactivity–impulsivity, and executive functioning of the participants from both the iMBI treatment and eTAU control groups will be assessed at baseline (week 0), immediate post-intervention (week 8), and 1-month follow-up (week 12).

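### The ITT analysis, run only if judged necessary, handles missing scores solely by last observation carried forward, which can bias the iMBI comparison in either direction at the expected 20% attrition

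*Protocol article*

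**What the plan says.** Four statements in the protocol article bear on this point.

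- Section 2.11 (Data Analysis) makes ITT conditional: "When necessary, study data will be analyzed using intention-to-treat analysis (ITT". It then fixes the handling of missing data under ITT: "the last observation carried forward method will be used to impute missing values or dropouts".
- The only other analysis named there is per-protocol: "We will perform per-protocol analysis to examine the effectiveness of iMBI when implemented in an optimal manner". The section gives no second missing-data method and no sensitivity analysis.
- The model in section 2.11 is a MANCOVA comparing the groups at both post-baseline visits, "simultaneously with baseline scores as covariates".
- Section 2.2 (Study Design) says outcomes "will be assessed at baseline (week 0), immediate post-intervention (week 8), and 1-month follow-up (week 12"), and section 2.5 (Sample Size) says: "The present study anticipates a 20% attrition rate, so a sample size of 54 participants per condition is needed, totaling 108 participants".

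**The concern.** Only one post-baseline visit, week 8, comes before the 1-month follow-up. For a participant lost during the programme, the only score available to carry forward is baseline. It fills both week 8 and week 12, which asserts exactly zero change in either arm. Baseline is also the covariate, so each imputed outcome equals its own covariate. For a participant lost after week 8, the week 8 score is copied into week 12, which asserts that nothing changed over the follow-up month. In both cases the filled-in values count as real data, so the standard errors ignore the missingness.

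Unequal dropout is plausible. One arm is asked for eight weekly sessions plus offline assignments (section 2.1.1). The other has one 30-minute webinar on top of usual care and is offered iMBI once data collection is over (section 2.1.2). If scores improve in both arms for general reasons, unequal loss under this method can hide a difference or create one. The estimate at stake is the one for the primary objective.

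**Working it through.** **The plan's own figure.** Section 2.5 needs 45 per condition and recruits 54. This reproduces as 45 × 1.20 = 54. (Dividing by 0.80 would give 57, which is a separate matter.) At 20% attrition, 0.20 × 54 = 10.8, so about 11 people per arm would have imputed scores.

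**Inputs.**
- From the protocol: 54 per arm, visits at weeks 0, 8 and 12, baseline as covariate, 20% attrition overall.
- Assumed, because the protocol gives no figure: a true effect δ of 0.60 SD (close to the 0.59 to 0.60 that 45 per arm at 80% power and two-sided 0.05 implies); correlation of 0.6 between baseline and outcome; a general improvement m in both arms; the split of dropout between arms; all dropout before week 8 and completely at random; dropouts would have had the full effect.

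**Expected estimate under LOCF.** With dropout p_T in the iMBI arm and p_C in control, dropouts contribute zero change, so

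estimate = (1 − p_T)(m + δ) − (1 − p_C)m = (1 − p_T)δ − (p_T − p_C)m.

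*True effect 0.60 SD, m = 0.5:*
- 20/20: 0.8 × 0.60 − 0 = 0.48 SD. This result does not depend on m.
- 30/10: 0.7 × 0.60 − 0.2 × 0.5 = 0.42 − 0.10 = 0.32 SD.

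*No true effect:*
- 30/10, m = 0.5: −0.2 × 0.5 = −0.10 SD, against iMBI.
- 10/30, m = 0.5: +0.10 SD, a false benefit.
- 25/15, m = 0.2: −0.1 × 0.2 = −0.02 SD.
- 20/20, any m: 0.

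**Simulated rejection rates** (about 4,000 trials per scenario; a single-outcome ANCOVA with baseline as covariate stood in for the MANCOVA):
- δ = 0.60, 20/20: 86 to 88% under LOCF, against 93 to 94% for ANCOVA on observed scores.
- δ = 0.60, 30/10, m = 0.5: 51% against about 92%.
- Null, m = 0.5, 30/10 or 10/30: about 10 to 11% under LOCF, against about 5% on observed scores.
- Null under LOCF, milder cases: 30/10 with m = 0.2, 5.6%; 25/15 with m = 0.5, 6.5%; 25/15 with m = 0.2, 5.1%; 20/20 with m = 0.5, 5.2%.

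**Loss after week 8.** Suppose the effect halves from 0.59 SD at week 8 to 0.295 SD at week 12, and 20% per arm are lost in between. LOCF then gives 0.8 × 0.295 + 0.2 × 0.59 = 0.354 SD at week 12. Simulation gave 0.355. Here LOCF overstates the effect.

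**The case against.** Several points on the other side have force.

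- **Scope.** A reader might infer that LOCF governs the main analysis. The text does not establish that. It ties LOCF to ITT and runs ITT conditionally, so which analysis is the main one is unclear. This narrows the point without removing it: wherever ITT is run, LOCF is the only method given.
- **Direction.** A reader might infer that LOCF manufactures a benefit for iMBI, or alternatively that it is safely conservative. Neither holds in general. If iMBI loses more people, the error runs against iMBI. A false benefit needs higher loss in control, and inflation at week 12 needs a waning effect.
- **Size.** The protocol gives one overall attrition figure, with no split by arm and no expected general improvement. The doubled type I error therefore belongs to one assumed scenario and is not a forecast. At 20% in each arm the simulated power stays above the planned 80%, and under the null there is no bias.
- **What counts as the truth.** The attenuation assumes that dropouts would have had the full benefit. If those who leave iMBI get only the general improvement, the effect in everyone randomised is 0.8 × 0.60 = 0.48 SD at 20/20. That equals the LOCF result, while the observed-data analysis reports 0.60. At 30/10 that truth is 0.7 × 0.60 = 0.42 SD: LOCF is 0.10 too low and the observed-data analysis 0.18 too high. This stands. It is the reason a missing-at-random analysis also needs a sensitivity analysis.
- **Follow-up after stopping.** Nothing in the protocol says that people who leave iMBI are no longer assessed, so there is no such defect to correct.

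**Conclusion.** The point holds for the ITT analysis. The protocol commits to a single-value imputation that is not valid under missing at random. With this visit schedule, it sets both outcomes equal to the covariate for anyone lost before week 8. Under the stated assumptions the distortion runs from nil (no effect, equal dropout), through about 0.02 SD (no effect, 25/15, 0.2 SD improvement), to about 0.10 SD in either direction with type I error of about 10 to 11% (no effect, 20-point imbalance, 0.5 SD improvement). With a real effect of 0.60 SD, the estimate falls by a fifth at equal 20% dropout and by nearly half at 30/10. The sign and size cannot be known in advance because they depend on which arm loses people, when, and how scores drift. The formula applies to any outcome at either visit when loss precedes week 8. The rejection rates come from a univariate ANCOVA, so they indicate the scale for the planned MANCOVA and are not exact for it.

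**What to change.** In section 2.11, state that the comparison of all randomised participants in their allocated arms is the main analysis, and remove the condition on ITT. Replace LOCF there with one method valid under missing at random:

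1. multiple imputation by arm feeding the planned MANCOVA, with the rule for pooling the multivariate test across imputed data sets written down; or
2. a likelihood-based repeated-measures model for weeks 8 and 12 (SPSS MIXED), with treatment by visit and baseline by visit, using all observed scores. If this route is taken, state what replaces the simultaneous test across outcomes.

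Keep LOCF at most as a sensitivity analysis. Add one missing-not-at-random sensitivity analysis, a delta adjustment in the iMBI arm, because people who leave the programme may not keep its benefit.

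The cost is revised wording and somewhat more analysis work in the software already named. The new main analysis would rest on a missing-at-random assumption, which the delta adjustment then probes. No more participants are needed.

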## 3. Discussion

The present study would have both theoretical and practical implications. With respect to theoretical implications, the present study may demonstrate the successful application of the executive dysfunction theory of ADHD in a Chinese Malaysian college sample. With respect to practical implications, the present study will inform practitioners on the effectiveness of iMBI and its potential in managing cognitive behavioral outcomes in emerging adults with ADHD. More work is necessary to increase the external validity of iMBI, with some suggestions offered as follows. First, only college students will be recruited in the present study. Given that dropout rates in high school among individuals with ADHD are high, high school ADHD patients may have greater functional impairment compared with college ADHD patients. Future studies examining the effectiveness of iMBI in reducing functional impairment in high school ADHD are needed. Second, participants from the eTAU control group may experience varied treatment-as-usual care, depending on the clinical wisdom of their treating clinicians. Future studies should focus on how varying treatment-as-usual conditions may result in different treatment effects. Last but not least, the present study will exclude individuals with significant comorbidity of psychiatric disturbances who may experience severe symptoms of ADHD. In future studies, recruiting adult ADHD with a different psychiatric comorbid diagnosis may be of benefit.

## 4. Conclusions

The findings of the present study will not only demonstrate the implementation of iMBI as a new treatment modality but also inform practitioners on the effectiveness of iMBI in reducing the burden of adults living with ADHD.

## Figures and Tables

**Figure 1 ijerph-18-01257-f001:**
[figure not shown]
Consolidated Standards of Reporting Trials (CONSORT) flow diagram.

**Table 1 ijerph-18-01257-t001:** Mapping of online mindfulness-based intervention to outcome variables.

Session	Outcome Variables		
	Inattention	Hyperactivity–Impulsivity	Executive Functioning
Session 1: Introduction to ADHD and Mindfulness	✓	✓	✓
Session 2: ADHD through the Lens of Mindfulness	✓	✓	
Session 3: Thinking, Noting, and Feeling	✓	✓	✓
Session 4: Mindful Awareness of Physical Sensation	✓		✓
Session 5: Mindfully Attend to Inattention	✓		✓
Session 6: Time Management with Mindfulness		✓	✓
Session 7: Mindful Awareness of Communication		✓	✓
Session 8: Review and Future Practices			✓
Total Number of Sessions	5	5	7

ADHD is Attention-deficit/hyperactivity disorder.

## Data Availability

Data sharing is not applicable to this study protocol.
